**Fig. 4 Fig4:**
[figure not shown]
Study participant time schedule of enrolment, interventions and assessments

### Primary outcomes

There are two primary outcomes corresponding to the study hypothesis.
The mean difference in PHQ-9 scores at 12 months will be assessed in the high-risk cohort.The difference in mean behaviour scores at 12 months using the Mental Health Knowledge, Attitude and Behaviour (KAB) scale will be analysed in the combined high-risk and non-high-risk cohort.

### Secondary outcomes

Remission (defined as all three of the following: PHQ-9 < 5, GAD-7 < 5 and suicide risk score < 2) in the high-risk cohort at 12 months.GAD-7 scores in the high-risk cohort at 12 monthsPHQ9 scores in the high-risk cohort at 6 monthsGAD7 scores in the high-risk cohort at 6 months.The proportion at high risk of CMDs at end of study who have visited a doctor at least once in the previous 12 months in the high-risk cohortThe difference in mean stigma scores at 12 months compared to baseline in the combined non-high-risk and high-risk cohortThe difference in mean knowledge and attitude scores and change in stigma perceptions at 12 months compared to baseline in the combined non-high-risk and high-risk cohort

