**Expected outcomes:**

The primary study outcome is the difference in mean behaviour scores at 12 months in the combined ‘high-risk’ and ‘non-high-risk’ cohort and the mean difference in PHQ-9 scores at 12 months in the ‘high-risk’ cohort. Secondary outcomes include depression and anxiety remission rates in the high-risk cohort at 6 and 12 months, the proportion of high-risk individuals who have visited a doctor at least once in the previous 12 months, and change from baseline in mean stigma, mental health knowledge and attitude scores in the combined non-high-risk and high-risk cohort. Trial outcomes will be accompanied by detailed economic and process evaluations.

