Non-physician health workers (ASHAs) are trained to use the PHQ-9 and GAD-7 to screen adults (≥ 18 years) in the village for CMDs. They use a tablet-based questionnaire to generate composite scores to identify ‘high-risk’ individuals.ASHAs can then provide basic supportive advice and a referral to the PHC doctor. Participants are electronically referred via the mHealth platform and provided with a paper referral card to take to the doctor.The PHC doctor then reviews participants as part of a village health camp visit or the patient can directly visit the PHC. Data from individuals are uploaded, with consent, to a secure health record using the OpenMRS open source, electronic health record system.A decision support application based on WHO’s mhGAP-IG algorithm is integrated in a tablet device and used by PHC doctors to diagnose and manage patients experiencing CMDs. Doctors can use the depression, self-harm/suicide and emotional or medically unexplained complaints’ modules of mhGAP-IG. Patients requiring medication can access these directly from the PHC or purchase low-cost generics from a private pharmacy.For people with complex needs, consultation with a specialist psychiatrist is available as needed. The psychiatrist can also conduct case reviews via phone and/or video conferencing with the PHC doctors to enhance their management skills. Alternatively, people can be referred by the PHC doctor to a psychiatrist in the next tier of the public health system.Mobile-based messages are sent to ASHAs to ensure adherence and follow-up of those individuals who are diagnosed with CMDs by PHC doctors. ASHAs are able to conduct follow-up visits and assess treatment adherence using a recall and reminder (priority listing) system installed on their mobile devices. ANMs will also assist in streamlining the referral system by ensuring that patients under treatment are regularly followed-up.An algorithm-based interactive voice response system is able to send out pre-recorded messages to diagnosed patients to continue care as advised by the PHC doctor and ASHA, and similar motivational messages can be sent to ASHAs to screen and follow up patients as per guidelines.

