## Research methods

### Study objectives

The study aims to evaluate the feasibility, clinical effectiveness and cost-effectiveness of a multifaceted primary healthcare worker intervention to identify and manage CMDs. The study hypothesises that SMART Mental Health will address mental healthcare access barriers and lead to significant improvements in community behaviours toward mental disorders, and improvements in the proportion of adults at high risk of CMDs achieving remission for depression, anxiety and suicide risk.

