#### High-risk cohort

Up to 165,000 adults will be screened until at least 150 individuals per PHC at high risk of CMDs have been identified. High risk is defined as the presence of at least one of the following:
High risk of depression based on PHQ-9 score ≥ 10.High risk of anxiety based on GAD7 score ≥ 10.Positive response (score ≥ 2) to the suicide risk question on the PHQ-9.

Given that there may be some time delay between screening and randomisation (at least 12 weeks), these participants will be rescreened to assess if they still meet the high-risk inclusion criteria prior to randomisation. The literature suggests that around 25% of people initially identified at high risk will no longer meet the high-risk criteria at 3 months [33], and consequently, we expect the final high-risk cohort to consist of at least 110 individuals per PHC.

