### Statistical considerations

Assuming a prevalence of 4% of adults with or at high risk of CMDs, we anticipate that around 165,000 adults in total (i.e. 3750 per PHC) will need to be screened at baseline to achieve the required sample size.

In the high-risk cohort, sample sizes of 1936 in intervention and 1936 in control (total 3872), obtained by sampling 22 clusters with an average of 88 subjects each in intervention group and 22 clusters with an average of 88 subjects each in control group at the end of trial, will provide 90% power to detect a standardised mean difference of 0.4 in PHQ-9. The sample size is based on pilot study estimates [5, 37] and ICC. The sample size is based on the primary outcome. These calculations assume an intra-class correlation coefficient (ICC) of 0.15, a coefficient of variation of cluster sizes of 0.65 and a two-sided significance level of 0.05. Power Analysis and Sample Size System (PASS) software licensed by NCSS has been used for sample size estimation.

In the non-high-risk cohort, although the primary outcome will be reported for the combined high-risk and non-high-risk cohort, the study is powered on each sub-group. Sample sizes of 1936 in intervention and 1936 in control (total 3872), obtained by sampling 22 clusters with an average of 88 subjects each in intervention group and 22 clusters with an average of 88 subjects each in control group at the end of trial, will provide > 90% power to detect a standardised mean difference of 0.3 in mean behaviour scores between the intervention and control arms in each cohort. Assuming a mean behaviour score of 2 (SD 1) at baseline, and a 20% relative improvement in the control group (score of 1.6) by 12 months based on pilot and published data [37], this corresponds to a 35% improvement in the intervention group (score of 1.3) and a between-group difference of 0.3 points. This assumes a conservative ICC of 0.05 (0.01 in pilot and 0.04 in similar studies) [37], and a 2-sided significance level of 0.05.

To allow for 20% loss to follow-up during the intervention, at least 110 individuals per PHC in the high-risk cohort and at least 110 individuals per PHC in the non-high-risk cohort will be recruited.

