Primary analyses will be conducted at the participant level using either random-effect models or generalised estimating equations adjusted for PHC clustering. For the primary outcome, the PHQ-9 score at 12 months, mean differences will be assessed using a linear regression including the intervention and the baseline PHQ-9 score as fixed effects and the cluster (PHC) as a random effect. If using generalised estimating equations, the effect of clustering will be accounted for using a repeated cluster effect with a compound-symmetry variance-covariance structure. The intervention effect will be estimated as the adjusted mean difference and corresponding 95% confidence interval. Subgroup analyses will be conducted according to PHC-level (size, location and health service characteristics) and patient-level characteristics (demographic factors and clinical factors, e.g. depression severity at baseline). Subgroup analyses will also be conducted to assess the difference in mean behaviour scores on KAB, at 12 months, separately for high-risk and non-high-risk cohort. Binary outcomes will be analysed similarly but using log-binomial or logistic regression in place of linear regression. A pre-specified analysis plan including sensitivity analyses, potential covariate adjustments, analyses for secondary endpoints and detailed assumptions (e.g. missing data handling) will be developed prior to unblinding and database lock.

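### Read literally, the doctor-visit secondary outcome counts only cohort members still at high risk at the end of the study, a status the intervention is meant to change; the abstract has no such condition

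*Protocol article*

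**What the plan says.** The Secondary outcomes list of the protocol article includes "The proportion at high risk of CMDs at end of study who have visited a doctor at least once in the previous 12 months", and the sentence ends by naming the high-risk cohort. The abstract, under Expected outcomes, gives the same item as "the proportion of high-risk individuals who have visited a doctor at least once in the previous 12 months", with no condition on risk status at the end of the study.

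Four other statements bear on this:

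- **When the cohort is fixed.** Under High-risk cohort, "these participants will be rescreened to assess if they still meet the high-risk inclusion criteria prior to randomisation". Membership is therefore settled before allocation.
- **What the intervention should do to risk status.** Study objectives hypothesises "improvements in the proportion of adults at high risk of CMDs achieving remission for depression, anxiety and suicide risk".
- **What it should do to visits.** Under mHealth-based EDSS, "ASHAs can then provide basic supportive advice and a referral to the PHC doctor".
- **How the outcome is analysed.** Statistical considerations says "Binary outcomes will be analysed similarly but using log-binomial or logistic regression in place of linear regression". Nothing there deals with selection on a status measured after randomisation.

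**The concern.** Two features of the outcome list favour the literal reading. The other outcomes confined to the high-risk cohort name that cohort once and give the timing as 6 or 12 months; only the doctor-visit item adds a second risk status. If that status meant baseline risk, it would merely repeat the cohort label at the end of the sentence.

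On the literal reading, a participant who sees a doctor and recovers leaves the denominator. High risk is a threshold status (PHQ-9 or GAD-7 of at least 10, or a suicide item score of at least 2), so a participant can leave without meeting the stricter remission definition. Leaving is not rare: the protocol expects about 25% of those first identified to lose high-risk status by 3 months, before any intervention.

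If recovery, and its link with visiting, differ between arms, the two groups compared are no longer those that randomisation created. At stake is the one listed outcome that measures contact with a doctor. A log-binomial or logistic model adjusted for clustering does not correct this kind of selection.

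**Working it through.** **The plan's own figures.** The protocol gives no rate, effect size or power for doctor visits. Its stated figure for the high-risk cohort is for PHQ-9: "will provide 90% power to detect a standardised mean difference of 0.4 in PHQ-9", with 22 clusters of 88 per arm (1936) and an ICC of 0.15.

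- With equal clusters the design effect is 1 + 87 × 0.15 = 14.05, and power is 91.3% (normal) or 90.0% (t, 42 df).
- Allowing for the stated coefficient of variation of 0.65 by relative efficiency (0.976) gives 90.7% or 89.3%, so the figure reproduces.
- A more conservative design effect for unequal clusters, 19.6, gives 80.2% or 78.4%.

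None of this bears on the definition of the visit outcome. Only the 1936 per arm is used below.

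**Formula.** In each arm let v be the probability of a visit, a the probability that a visitor is still at high risk at 12 months, and b the same for a non-visitor. The whole-cohort proportion is v. The proportion among those still at high risk is

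v·a / [v·a + (1 − v)·b].

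**Inputs.** Every v, a and b below is an assumption. The cases are chosen to show the range.

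| Case | Intervention (v, a, b) | Control (v, a, b) | Whole cohort | Still at high risk |
|---|---|---|---|---|
| 1. Recovery unrelated to visiting | 0.5, 0.5, 0.5 | 0.3, 0.6, 0.6 | +20 | +20 |
| 2. Visits equally effective in both arms | 0.5, 0.3, 0.6 | 0.3, 0.3, 0.6 | +20 | +15.7 |
| 3. No effect on visits; intervention visits work better | 0.4, 0.3, 0.7 | 0.4, 0.6, 0.7 | 0 | -14.1 |
| 4. Visits lead to recovery much more often in intervention | 0.5, 0.2, 0.6 | 0.3, 0.6, 0.6 | +20 | -5 |

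Differences are in percentage points, intervention minus control.

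- Case 1: 0.25/(0.25 + 0.25) = 50.0%; 0.18/(0.18 + 0.42) = 30.0%.
- Case 2: 0.15/(0.15 + 0.30) = 33.3%; 0.09/(0.09 + 0.42) = 17.6%.
- Case 3: 0.12/(0.12 + 0.42) = 22.2%; 0.24/(0.24 + 0.42) = 36.4%.
- Case 4: 0.10/(0.10 + 0.30) = 25.0%; 0.18/(0.18 + 0.42) = 30.0%. The denominators are 0.4 × 1936 ≈ 774 and 0.6 × 1936 ≈ 1162.

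**Bias in the other direction.** Suppose each arm has two equal severity groups, with visit rates of 30% (milder) and 50% (more severe) in both arms, so the true difference is 0. Let 20% and 60% remain at high risk in the intervention arm, and 50% and 70% in control, with recovery unrelated to visiting within each group.

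- Intervention: (0.5 × 0.3 × 0.2 + 0.5 × 0.5 × 0.6)/0.40 = 0.18/0.40 = 45.0%.
- Control: (0.5 × 0.3 × 0.5 + 0.5 × 0.5 × 0.7)/0.60 = 0.25/0.60 = 41.7%.

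The spurious difference is now +3.3 points, in favour of the intervention.

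**A third parsing.** If the sentence means the share of the whole cohort that both visited and is still at high risk, the denominator is randomised, but the measure mixes visiting with failure to recover. In case 4 it is 0.5 × 0.2 = 10% against 0.3 × 0.6 = 18%.

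**The case against.** The best defence is that the end of the study is only the time of asking. The sentence closes by naming the high-risk cohort, which is the population label used throughout the list and is fixed before randomisation. The protocol also uses the high-risk description for baseline status elsewhere: the study hypothesis speaks of people at high risk achieving remission, and someone in remission is by definition no longer at high risk. The abstract, with no end-of-study condition, fits this reading. The defence stands to this extent: a reader might infer that the sponsor chose to condition on a post-randomisation variable, and the text does not establish that. It establishes two wordings that select different people.

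A second objection is that the sign change and the direction of bias rest on chosen rates. That also stands. A reader might infer that the outcome is bound to be biased against the intervention, or that a reversal is to be expected. Neither follows: a reversal needs visits to lead to recovery much more often in the intervention arm, and the severity example moves the other way.

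A third objection is that the protocol defers the analysis of secondary endpoints to a later plan. This carries less weight, because the outcome itself is defined here, in two ways that do not agree.

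**Conclusion.** The point holds as a defect of definition, at moderate confidence. Followed literally, the Secondary outcomes wording compares arms within a group selected on a consequence of treatment. The abstract does not.

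Under assumed rates, the distortion runs from nil when recovery is unrelated to visiting, through attenuation from +20 to +15.7 points when visits work equally well in both arms, to a spurious -14 points or a reversal from +20 to -5 points when visits lead to recovery much more often in the intervention arm. These figures show what could happen; they are not estimates for this trial.

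It would be too strong to call this a fault in the trial's main process measure. The protocol does not give the outcome that rank; it is one of several secondary outcomes. Both primary outcomes, the remission outcome and the sample size are untouched. It should be fixed, but it does not threaten the main conclusions.

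**What to change.** Use one definition in both the Secondary outcomes list and the abstract: the proportion of all participants in the baseline high-risk cohort, whatever their risk status at 12 months, who visited a doctor at least once in the 12 months after randomisation, compared between arms. The binary-outcome model already named can be kept.

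The cost is one sentence in each place. The whole cohort is already followed to 12 months, so no new follow-up is needed, provided the visit question is put to every cohort member and not only to those who still meet the high-risk criteria. The denominator can only stay the same or grow. If visits among people still at high risk are also of interest, they can be reported by arm as a description, labelled as not a randomised comparison.

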### Statistical considerations

Assuming a prevalence of 4% of adults with or at high risk of CMDs, we anticipate that around 165,000 adults in total (i.e. 3750 per PHC) will need to be screened at baseline to achieve the required sample size.

In the high-risk cohort, sample sizes of 1936 in intervention and 1936 in control (total 3872), obtained by sampling 22 clusters with an average of 88 subjects each in intervention group and 22 clusters with an average of 88 subjects each in control group at the end of trial, will provide 90% power to detect a standardised mean difference of 0.4 in PHQ-9. The sample size is based on pilot study estimates [5, 37] and ICC. The sample size is based on the primary outcome. These calculations assume an intra-class correlation coefficient (ICC) of 0.15, a coefficient of variation of cluster sizes of 0.65 and a two-sided significance level of 0.05. Power Analysis and Sample Size System (PASS) software licensed by NCSS has been used for sample size estimation.

In the non-high-risk cohort, although the primary outcome will be reported for the combined high-risk and non-high-risk cohort, the study is powered on each sub-group. Sample sizes of 1936 in intervention and 1936 in control (total 3872), obtained by sampling 22 clusters with an average of 88 subjects each in intervention group and 22 clusters with an average of 88 subjects each in control group at the end of trial, will provide > 90% power to detect a standardised mean difference of 0.3 in mean behaviour scores between the intervention and control arms in each cohort. Assuming a mean behaviour score of 2 (SD 1) at baseline, and a 20% relative improvement in the control group (score of 1.6) by 12 months based on pilot and published data [37], this corresponds to a 35% improvement in the intervention group (score of 1.3) and a between-group difference of 0.3 points. This assumes a conservative ICC of 0.05 (0.01 in pilot and 0.04 in similar studies) [37], and a 2-sided significance level of 0.05.

To allow for 20% loss to follow-up during the intervention, at least 110 individuals per PHC in the high-risk cohort and at least 110 individuals per PHC in the non-high-risk cohort will be recruited.

Primary analyses will be conducted at the participant level using either random-effect models or generalised estimating equations adjusted for PHC clustering. For the primary outcome, the PHQ-9 score at 12 months, mean differences will be assessed using a linear regression including the intervention and the baseline PHQ-9 score as fixed effects and the cluster (PHC) as a random effect. If using generalised estimating equations, the effect of clustering will be accounted for using a repeated cluster effect with a compound-symmetry variance-covariance structure. The intervention effect will be estimated as the adjusted mean difference and corresponding 95% confidence interval. Subgroup analyses will be conducted according to PHC-level (size, location and health service characteristics) and patient-level characteristics (demographic factors and clinical factors, e.g. depression severity at baseline). Subgroup analyses will also be conducted to assess the difference in mean behaviour scores on KAB, at 12 months, separately for high-risk and non-high-risk cohort. Binary outcomes will be analysed similarly but using log-binomial or logistic regression in place of linear regression. A pre-specified analysis plan including sensitivity analyses, potential covariate adjustments, analyses for secondary endpoints and detailed assumptions (e.g. missing data handling) will be developed prior to unblinding and database lock.

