### Randomisation

Cluster randomisation will occur at the level of the PHC. A total of 44 PHCs from West Godavari district of Andhra Pradesh and Faridabad and Palwal districts of Haryana will be selected. Allocation of PHCs (including 2–5 villages per PHC) to intervention or control arm will use a computer-generated 1:1 central allocation sequence. Random allocation for PHC will be performed using SAS PROC plan or another relevant procedure. PHCs at each site will be stratified by natural remission rate after the initial screening is completed, and population size of the PHCs. To maintain blinding, the unblinded statistician will generate the actual randomisation list and share with field staff. The blinded statistician on the study will work with dummy treatment arms until the end of study. The treatment-related columns will not be shared with blinded statistician/statistical team until the time of planned study unblinding.

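### The stated primary PHQ-9 model leaves out the strata used to randomise PHCs; if those strata are prognostic, its standard error is too large and the test is conservative

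*Protocol article*

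**What the plan says.** Randomisation: the PHC is the unit, and allocation "will use a computer-generated 1:1 central allocation sequence". The section continues: "PHCs at each site will be stratified by natural remission rate after the initial screening is completed, and population size of the PHCs". It does not give the number of levels of each factor, define the natural remission rate, or say why it was chosen.

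Statistical considerations, analysis paragraph: the PHQ-9 score at 12 months is to be analysed by linear regression "including the intervention and the baseline PHQ-9 score as fixed effects and the cluster (PHC) as a random effect". The alternative by generalised estimating equations names no stratum terms either. PHC size and location appear only as subgroup factors. For the behaviour score the article gives no covariate list. The paragraph ends by promising "A pre-specified analysis plan including sensitivity analyses, potential covariate adjustments, analyses for secondary endpoints" and further detail before unblinding and database lock.

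Statistical considerations, sample size: the PHQ-9 calculation uses "22 clusters with an average of 88 subjects each in intervention group" and the same number in the control group. It states that this "will provide 90% power to detect a standardised mean difference of 0.4 in PHQ-9". "These calculations assume an intra-class correlation coefficient (ICC) of 0.15", with "a coefficient of variation of cluster sizes of 0.65" and a two-sided level of 0.05. No gain from stratification is claimed.

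**The concern.** Stratified allocation balances the arms on the stratifiers, so between-stratum differences drop out of the true sampling error of the arm contrast. A model without the strata does not know this. It leaves those differences in the PHC random-effect variance and reports a standard error that includes them. Intervals are then too wide and the test rejects less often than its nominal level.

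The effect could matter here because, at an ICC of 0.15 with 88 people per PHC, almost all the variance of a PHC mean lies between PHCs. Any share that the strata explain therefore passes nearly undiluted into the standard error. Significance also has a consequence in this plan. The Economic evaluation section makes the choice between a decision-analytic model and a cost-minimisation analysis depend on whether the primary outcomes differ significantly.

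**Working it through.** **1. The plan's own figure.** Inputs from the sample-size text: 22 PHCs per arm, m = 88 (1936 per arm), ICC 0.15, CV 0.65, difference 0.4 SD.

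- L = 88 × 0.15 / (88 × 0.15 + 0.85) = 13.2 / 14.05 = 0.9395.
- Design effect = [1 + 87 × 0.15] / [1 − 0.65² × L(1 − L)] = 14.05 / 0.976 = 14.40.
- SE = √(2 × 14.40 / 1936) = 0.1219.
- Power = 90.7% (normal) or 89.3% (t, 42 df).
- With equal clusters the design effect is 14.05, the SE 0.1205, and power 91.3% (normal) or 90.0% (t).

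The stated 90% is reproduced without any stratum adjustment. The design effect 1 + [(CV² + 1)m − 1] × ICC = 19.63 gives 80.2% and does not reproduce it, so it is not used below.

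**2. Where the variance lies.** The variance of a PHC mean is 0.15 + 0.85/88 = 0.1597. The between-PHC share is 0.15 / 0.1597 = 94%.

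**3. Closed form, equal clusters.** Let f be the share of between-PHC variance that the strata explain beyond baseline PHQ-9. The protocol gives no value, so f is an assumption. With balanced allocation within strata, the true SE is √{(4/44) × [0.15(1 − f) + 0.85/88]}. The model without strata still reports about 0.1205.

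| f | True SE | Reported / true | CI width, unadjusted / adjusted |
|---|---|---|---|
| 0 | 0.1205 | 1.00 | 0.99 |
| 0.1 | 0.1147 | 1.05 | 1.04 |
| 0.2 | 0.1086 | 1.11 | 1.10 |
| 0.3 | 0.1021 | 1.18 | 1.17 |

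The last column multiplies the SE ratio by 2.018/2.030, the t quantiles on 42 df (44 − 2) and 35 df (44 − 9, for 8 strata and arm).

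**4. Simulation on PHC means** (44 PHCs, 8 assumed strata, ICC 0.15, m = 88, difference 0.4 SD).

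| f | Type I error, unadjusted | Power, unadjusted | Power, adjusted | Loss (points) |
|---|---|---|---|---|
| 0 | 5.0% | 90.0% | 89.6% | −0.4 |
| 0.1 | 4.0% | 91.3% | 92.4% | 1.1 |
| 0.2 | 3.3% | 92.2% | 94.6% | 2.4 |
| 0.3 | 2.4% | 93.5% | 96.9% | 3.4 |

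The adjusted model holds its level at about 5% throughout. Simulated intervals are about 5% wider at f = 0.1, 9% at f = 0.2 and 16% at f = 0.3. How the stratum effects are generated shifts these figures a little. With effects held fixed, f = 0.3 gives a mean SE of 0.1206 against 0.1015, so the interval is 0.1206/0.1015 × 2.018/2.030 = 1.18 times as wide. Type I error is then 2.2% and power 93.3% against 96.5%.

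**5. Behaviour score at its planned inputs** (difference 0.3 SD, ICC 0.05, 88 per PHC). Power is 98.4% against 99.0% at f = 0.2, and 98.8% against 99.4% at f = 0.3. The loss is about 0.6 points.

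**The case against.** The strongest reply is deferral. The same paragraph leaves covariate adjustments to an analysis plan that is not shown, and it has not even settled between random-effects models and generalised estimating equations. That plan may already contain the strata. This stands as a reason to ask for confirmation, but it does not remove the point. The fixed effects of the PHQ-9 model are listed, the stratifiers are not among them, and a reference to potential adjustments commits to none. For the behaviour score the reply succeeds: no covariates are listed, so nothing there can be said to leave the strata out.

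The second reply is that the strata may not be prognostic. A reader might infer that natural remission rate was chosen because it predicts 12-month PHQ-9, but the protocol gives no reason. If the rate means the share who no longer meet the high-risk criteria at rescreening, it describes people who have left the analysed cohort. Whether it predicts outcome in those who remain, given their baseline score, is unknown. On the other side, an individual's baseline PHQ-9 does not obviously carry a PHC-level recovery rate or the difference between two states. The size of the effect therefore has to stay conditional.

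Third, the calculations leave out baseline PHQ-9 and, in the simulation, the variation in cluster size. They also assume 8 strata. The figures illustrate the effect and do not predict it.

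**Conclusion.** The point holds as a conditional loss of efficiency. The stated PHQ-9 model does not reflect the stratified randomisation. If the strata explain 10 to 30% of between-PHC variance beyond baseline PHQ-9, the interval is about 5 to 16% too wide, type I error is about 4.0 to 2.4%, and power at 0.4 SD is about 1 to 3 points below what adjustment would give. If they explain nothing, there is no loss. The share and the 8 strata are assumptions.

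The documents do not support several stronger readings that a reader might infer:

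- That the primary result would be biased or falsely positive too often. The error runs in the conservative direction.
- That the trial falls short of its planned power. The 90% was computed without any stratum gain, and the unadjusted analysis reaches it at every share examined.
- That stratifying brings no return without adjustment. Unadjusted power rises from 90.0% to 93.5% as the share goes from 0 to 30%.
- That much larger power gaps arise at a difference of 0.3 SD. Those need an ICC of 0.15, whereas the plan pairs 0.3 with an ICC of 0.05, where the loss is under 1 point.

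**What to change.** Before unblinding, write the primary PHQ-9 model with site, natural-remission stratum and PHC-size stratum as fixed effects beside intervention, baseline PHQ-9 and the PHC random effect. Carry the same terms into the generalised estimating equations if that route is taken. Specify the same stratum terms for the behaviour score, whose covariates the article leaves open. Keep the model without strata as a sensitivity analysis. If the analysis plan already does this, a sentence confirming it is enough.

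The cost is wording and a few cluster-level degrees of freedom: at most 7 with the 8 assumed strata (42 − 35), and fewer if the factors enter as main effects. If the strata explain nothing, this amounts to about 0.3 to 0.5 points of power.
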